## 8 Participant Entry

### 8.1 PRE-REGISTRATION EVALUATIONS

Medical history and current health issues will be evaluated. Sleepiness will be assessed by means of the Stanford Sleep Disorders Questionnaire and the Epworth sleepiness scale. A physical examination including weight, height, blood pressure and cardio-pulmonary auscultation will be performed.

### 8.2 INCLUSION CRITERIA

- Healthy, i.e. absence of any previous or current medical condition other than minor intercurrent medical issues or accidents that do not interfere with current health status or physical performance. No current medical treatment.
- male gender (inclusion of females is not feasible because it would require to control for the effects of the menstrual cycle on ventilation and various other physiological processes).
- age 20-70y
- residence at <800m
- informed consent.

### 8.3 EXCLUSION CRITERIA

- Any active disease or health related condition requiring treatment (in particular, sleep apnea and other sleep disorders, chronic rhinitis, cardiovascular and lung disease)
- body mass index <18 or >30 kg/m^2
- use of drugs that affect respiratory center drive (benzodiazepines or other sedatives, sleep inducing drugs, morphine or codeine derivatives), stimulants (modafinil, methylphenidate, theophylline), or illicit drugs
- Previous intolerance of moderate altitude (<3000m) due to acute mountain sickness, altitude related cerebral or pulmonary edema requiring unplanned descent, medical treatment or evacuation
- Exposure to altitudes >1500m for >1 day within the last 2 weeks before the study
- salbutamol-/nitroglycerin-intolerance
- Regular consumption of recreational drugs including alcohol and nicotine

### 8.4 WITHDRAWAL CRITERIA

Any active or unstable disease leads to exclusion from our study. Consumption of alcohol, illicit drugs, medication as described above or any unruly behavior or failure to follow the study protocol leads also to exclusion. Participants can withdraw from the study anytime without reason.

## 9 Efficacy and Safety Variables

### 9.1 EFFICACY VARIABLES

#### 9.1.1 Symptom evaluation

Subjective sleep quality will be evaluated by a visual analog scale. Subjective sleepiness will be evaluated by the Stanford Sleep Disorder Questionnaire. Symptoms of acute mountain sickness will be evaluated by the Environmental Symptoms Questionnaire cerebral score (AMS-c).

#### 9.1.2 Sleep and breathing

##### 9.1.2.1 Polysomnography

Nocturnal polysomnography are performed according to standard techniques as described previously. In addition to central EEG derivations, EOG and submental EMG, measurements include calibrated respiratory inductive plethysmography (RespiratracePT, Nims, Miami Beach, USA), pulse oximetry, end-tidal (CapnoCheck Plus, ResMed, Basel Switzerland) and transcutaneous PCO2 (Tosca, Radiometer, Basel, Switzerland), pulse transit time, nasal airflow estimated by nasal prongs connected to a pressure transducer, oral thermistor, bilateral sub costal surface EMG of the diaphragm^22 to assist in differentiation of obstructive from central apnea/hypopnea. Sleep and arousals will be scored according to standard criteria as described by Rechtschaffen und Kales and by the American Academy of Sleep Medicine guidelines. An apnea or hypopnea will be scored if the amplitude of the nasal pressure swings or the sum signal of the respiratory inductive plethysmography falls below 50% of baseline during the previous 2 minutes for >10 seconds.

##### 9.1.2.2 Pulmonary function testing

In order to detect subclinical High Altitude Pulmonary Edema Spirometry including diffusion capacity will be performed according to standard techniquesA3, A4. In cases of subclinical HAPE vital capacity as well as the diffusion capacity will be reduced due to increased intrapulmonary fluid accumulation.

A3) ATS/ERS task force. Standardization of spirometry. Eur Respir J 2005;26:319-338.

A4) ATS/ERS task force. Standardization of the single breath uptake of carbon monoxide in the lung. Eur Respir J 2005;26:720-735. A2) O. Senn et al.. Med Sci.Sports Exerc. 38 (9):1565-1570, 2006.

#### 9.1.3 Vigilance and psychomotor performance

These tests as described below provide multiple, well defined parameters of psychomotor performance that are sensitive to sleep. In addition, driving and snow board simulators are used to evaluate complex and realistic skill performance. All tests will be performed in a quiet room with subjects wearing sound protective ear covers. The light in the room will be dimmed.

#### **9.1.3.1 Psychomotor Vigilance Test (PVT)**

Vigilance will be assessed by the Psychomotor Vigilance Test (PVT) which is sensitive for effects of sleep restriction/disturbance and hypoxia. As described by Dinges et al the PVT measures the reaction time to a visual stimulus (LED) presented in variable intervals between 1 to 10 s over a period of 10-15 min. The subjects respond by pressing a button on a hand-held device (Stowood Scientific Instruments Ltd., Oxford).

#### **9.1.3.2 Motor Task Manager (MTM)**

The MTM requires the subjects to move a cursor with a hand on the digitizing surface while their hand position and target locations are displayed on a computer screen. A computer program reports the main extracted parameters such as performed trajectories; speed, acceleration and jerk profiles, directional error, linear error and time error. (ETT s.r.l., Genova)

#### **9.1.3.3 Divided Attention Driving Simulator (DADS)**

The DADS is a personal computer based driving simulation test. While driving down the abstract image of a winding road, random single digit numbers will be displayed at the screen corners. Subjects are required to confirm the appearance of the number '2' in addition to keeping the virtual car on track. (SimDrive, Divided Attention Driving Simulator, Stowood Scientific Instruments, Oxford, UK). Outcomes are mean distance from center (mean error), SD of mean distance from center, number of off-road events, reaction time (time to response to digit 2).

#### **9.1.3.4 Snowboarding Simulation**

A commercial entertainment system developed by Nintendo Co is being used to test the motor performance by means of manufacturer provided and custom software with the snowboarding simulation game. With the balance board (a platform equipped with 4 gravity sensors upon which the subjects stand) this system provides a reliable, scientifically evaluated assessment for balance. The Nintendo System compares favorably to 'gold standard' laboratory grade force-platforms (Nintendo Wii fit plus with balance board, Nintendo Co., Ltd, Kyoto, Japan).

### **9.1.4 Cardiovascular function**

To assess autonomic function, measures of heart rate variability (SD, low/high frequency spectral power) derived by ECG during polysomnography will be analyzed.

#### **9.1.4.1 Augmentation index (AIx) measured by pulse wave analysis**

Pulse wave analysis is a technique which uses applanation tonometry to assess the arterial pressure waveform. The pressure within an artery is a composite of both the forward ejected wave and the reflected waves travelling back to the heart. In healthy arteries, the reflected waves travel slowly and reach the heart in diastole thereby enhancing coronary perfusion. If the vasculature is stiffened, the reflected waves travel faster and reach the heart in systole, thus

augmenting systolic pressure. Systemic arterial stiffness can be measured using augmentation index (AIx), calculated as the difference between the second systolic peak and inflection point, expressed as a percentage of the central pulse pressure. AIx decreases in response to vasodilators (e.g. nitro-glycerine, salbutamol) by reduction of smooth muscle tone, and it has been demonstrated that AIx falls following inhaled salbutamol as a result of endothelial dependent nitric oxide release. Therefore, an impaired decrease of AIx after inhalation of salbutamol is a display of endothelial dysfunction. Pulse wave analysis is performed with a micro manometer (SphygmoCor, At-Cor Medical) which records radial artery pulse waveforms continuously. Mean values of approximately 10 pulse waves are used for analyses. A validated transfer function is used to generate a corresponding central aortic pressure waveform as described previously and AIx is then calculated. After a baseline recording, salbutamol is administered by inhalation (400 µg), and a re-evaluation of the pulse wave is performed after 10 minutes. Endothelial independent vasodilatation is assessed by pulse wave analysis as described above 3 minutes after sublingual application of nitro-glycerine 0.5 mg.

#### **9.1.4.2 Blood Markers of inflammation, cardiovascular function and insulin sensitivity**

Blood will be drawn in the mornings after each sleep study, centrifuged and resulting plasma samples will be stored at -80 °C for later analysis. The Dade Behring BN method (particle-enhanced immunonephelometry, detection limit 0.18 mg/L, measuring range 0.18-1150 mg/L) will be used to measure HsCRP as previously described and validated. IL-6, TNF-α (inflammatory cytokines) and TGF-β (anti-inflammatory cytokine) will be measured by highly sensitive ELISA with commercially available kits (Bender MedSystems GmbH, Vienna, Austria) with a lower limit of detection of 0.1 pg/ml. Brain natriuretic peptide (BNP), fasting insulin and glucose as well as cell-derived micro particles will be measured as previously described.

## **9.2 SAFETY VARIABLES**

Adverse events or reactions will be evaluated by daily physical examinations, evaluation of questionnaires, through the acquisition of the variables described above and through voluntary report.

## 10 Adverse events

### 10.1 DEFINITIONS

#### 10.1.1 Adverse Event (AE):

Any untoward medical occurrence in a study participant, whether or not related to the study, will be recorded. Each participant will be examined according to checklists and with questionnaires during the study. Adverse events will be recorded in prepared forms and checklists (see CRF).

#### 10.1.2 Serious Adverse Event (SAE):

Any untoward and unexpected medical occurrence or effect that:

- Results in death,
- Is life-threatening – refers to an event in which the subject was at risk of death at the time of the event; it does not refer to an event which hypothetically might have caused death if it were more severe,
- Requires hospitalisation, or prolongation of existing inpatients' hospitalisation,
- Results in persistent or significant disability or incapacity,
- Is a congenital anomaly or birth defect.
- Medical judgement should be exercised in deciding whether an AE is serious in other situations. Important AEs that are not immediately life-threatening or do not result in death or hospitalisation but may jeopardise the subject or may require intervention to prevent one of the other outcomes listed in the definition above, should also be considered serious.

SAEs will be immediately reported to the Ethics committee of the Canton Zürich. A special form will be completed. Patients will be followed until the event resolves or until 12 weeks after the event is reported.

An emergency action plan will be prepared with instructions on first aid and evacuation. In case of an emergency at Davos Jakobshorn the patient will receive first aid and treatment and will be evacuated to the hospital of Davos if necessary. Descent by cable car is available for emergencies also at nighttimes. First aid materials will be readily available at all study locations.

Since this is a physiologic study in healthy subjects no serious or clinically relevant adverse effects are expected. Light forms of Acute Mountain Sickness with symptoms such as headache, light-headedness, fatigue and insomnia may occur. More severe symptoms are unlikely because of the moderate altitude. Nevertheless, oxygen administration to reverse hypoxia and subsequent descent to lower altitude may be performed in case of emergencies. Skin irritation may appear due to attachments of the sensors. Venous blood will be drawn by a physician. Minor pain and hematoma at the puncture site may occur. A first aid kit with medication for treatment of altitude related illness and for skin irritation and hematoma from venipuncture will be readily available.

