## **10.2 REPORTING PROCEDURES**

All adverse events will be reported. Depending on the nature of the event the reporting procedures below should be followed. Any questions concerning adverse event reporting will be directed to the Principal Investigator in the first instance.

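### Section 10.1.2 makes 'unexpected' part of the SAE definition, which conflicts with section 10.2.2, where expectedness is judged only later, to pick out SUSARs

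*Protocol*

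**What the plan says.** Section 10.1.1 sets no expectedness condition for an ordinary adverse event: "Any untoward medical occurrence in a study participant, whether or not related to the study, will be recorded". Section 10.1.2 does set one for a serious event. Its opening line reads "Any untoward and unexpected medical occurrence or effect that", and the usual seriousness criteria follow, ending with a bullet that leaves other important events to medical judgement.

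The same section attaches duties to SAE status. One is prompt notice: "SAEs will be immediately reported to the Ethics committee of the Canton Zürich". Another, besides completion of a dedicated form, is continued observation: "Patients will be followed until the event resolves or until 12 weeks after the event is reported". The section also says what is anticipated in this study. Its general statement for these healthy volunteers is that "no serious or clinically relevant adverse effects are expected". On mountain sickness it allows for mild cases only: "Light forms of Acute Mountain Sickness with symptoms such as headache, light-headedness, fatigue and insomnia may occur". As to worse cases, its view is that "More severe symptoms are unlikely because of the moderate altitude". Irritated skin under the sensors, and minor pain or hematoma after venipuncture, are named as well.

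Section 10.2 states generally that "All adverse events will be reported" and then divides procedures by seriousness. Under 10.2.1, non-serious events are recorded regardless of expectedness. Under 10.2.2, an SAE form goes to the Principal Investigator within 24 hours. The Principal Investigator then assesses relatedness and expectedness, the latter by whether the protocol lists the event as expected. SAEs that are both related and unexpected are SUSARs, with 15-day reporting, or 7-day reporting if fatal or life-threatening. Section 11.3 provides for no general follow-up.

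**The concern.** Seriousness and expectedness are separate properties. Seriousness decides whether an event enters expedited handling. Expectedness, judged afterwards, decides whether a related serious event is also a SUSAR. Section 10.2.2 follows that order. Section 10.1.2 does not, because it makes expectedness a condition of entry, and only for serious events.

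At stake is the handling of any serious event that someone classes as expected. Under the literal definition it is not an SAE, yet it is not a non-serious event either. It would still be recorded under 10.1.1 and reported in the general sense of 10.2, but those sections give no recipient or deadline for it. The participants are healthy volunteers, and nothing else in the protocol replaces the SAE follow-up rule, so the definition should not depend on inference.

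**Working it through.** No rate or sample-size arithmetic applies. The check sets the sections against each other and counts what depends on the definition.

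**1. Are the two rules consistent?**
- 10.1.2: SAE = untoward, and unexpected, and meeting a seriousness criterion.
- 10.2.2: SUSAR = SAE, and related, and unexpected.
- Substituting the first into the second makes 'unexpected' redundant in the SUSAR rule. The expectedness assessment in 10.2.2 has a purpose only if expected SAEs can exist, and 10.1.2 says they cannot. Both rules stand in the current text.

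**2. Which events are affected?**
- Serious and unexpected: an SAE under both sections, so no conflict.
- Non-serious: handled under 10.2.1 whether expected or not, so no conflict.
- Serious and expected: not an SAE under 10.1.2, but an SAE that is not a SUSAR under the logic of 10.2.2. This is the only affected class.

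**3. What would that class lose?**
- Immediate ethics committee notice (10.1.2): lost on the literal definition.
- Follow-up to resolution or 12 weeks (10.1.2): lost on the literal definition, and 11.3 supplies no substitute.
- SAE form within 24 hours (10.2.2): arguably kept. It stands under a heading for serious events and comes before the expectedness judgement.
- 15-day and 7-day SUSAR reports (10.2.2): nothing lost, because they require an unexpected event in any case.
- First aid, oxygen, descent and evacuation (10.1.2): not tied to SAE status.

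So 2 duties clearly depend on the faulty definition, and a third is arguable.

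**4. How large is the class?**
- Effects named as possible: 4 (light mountain sickness, skin irritation, minor puncture pain, hematoma).
- Serious as described: 0 of 4.
- With a more severe form discussed in section 10.1.2: 1 of 4 (mountain sickness), and that form is called unlikely.

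To place a serious event in the class, someone would have to treat a severe form as listed because its light form is listed, or because altitude illness is discussed elsewhere (section 5.1 asks whether pulmonary edema occurs at 2590 m, and section 9.1.2.2 tests for its subclinical form). Neither is a listing of a serious effect as expected.

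**The case against.** The strongest answer is that the affected class is close to empty. Expectedness under 10.2.2 means being listed as expected, and the protocol says "no serious or clinically relevant adverse effects are expected". Severity is built into the list itself: mountain sickness is listed in light forms, and puncture-site pain as minor. A participant hospitalised with mountain sickness does not have a light form, so the event is unlisted, hence unexpected, hence an SAE under both sections. The statement "More severe symptoms are unlikely because of the moderate altitude" is hard to read as making severe symptoms expected. All of this stands, and it limits the consequence sharply.

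The order of steps in 10.2.2 also works in the protocol's favour. Staff who follow it would send the form before anyone judges expectedness. That too stands, and it is why the 24-hour form should not be counted as clearly lost.

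The final bullet of 10.1.2, on medical judgement, helps less. It sits under the same opening line and concerns important events that are not immediately life-threatening and do not lead to death or hospitalisation, so it does not bring back a hospitalised case judged expected.

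The objection does not remove the conflict. If serious events are always unexpected here, the expectedness test in 10.2.2 does nothing, and correct handling rests on an inference that the definition does not state.

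**Conclusion.** The definition in section 10.1.2 is wrong as written and contradicts section 10.2.2. That much is certain from the text. The consequence is minor. On a literal reading, a serious event judged expected would miss the immediate ethics committee notice and the follow-up to resolution or 12 weeks. Realistically this could concern only a severe form of altitude illness, and only on a strained reading of what is listed.

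A reader might infer more: that every expedited step is lost, including the 24-hour form and the SUSAR reports, or that hospitalised mountain sickness is likely to go unreported. The documents do not support that. The form is arguably still required under 10.2.2, SUSAR reporting needs an unexpected event in any case, and no serious effect is listed as expected. Emergency care and efficacy results are unaffected.

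This rests on the protocol text alone. The case report form, which section 10.1.1 says holds the adverse event forms, is not at hand and may word the definition differently.

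**What to change.** Delete 'and unexpected' from the first line of section 10.1.2, so that an SAE is defined by seriousness alone, and keep expectedness only in 10.2.2 as the test for SUSARs. This resolves the conflict completely.

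Optionally, add a sentence to 10.2.2 saying that a listed effect counts as expected only in its listed light or minor form. This mostly restates limits already in the list and is not needed for consistency.

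The cost is a two-word deletion, with no new form, visit or procedure. The downside is at most a rare extra report to the ethics committee.

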## **10.2 REPORTING PROCEDURES**

All adverse events will be reported. Depending on the nature of the event the reporting procedures below should be followed. Any questions concerning adverse event reporting will be directed to the Principal Investigator in the first instance.

### **10.2.1 Non serious AEs**

All such events, whether expected or not, will be recorded.

### **10.2.2 Serious AEs**

A SAE form will be completed and forwarded to the Principal Investigator within 24 hours.

The Principal Investigator will assess whether the event is:

- ‘related’, i.e. resulted from the administration of any of the research procedures; and
- ‘unexpected’, i.e. an event that is not listed in the protocol as an expected occurrence.

Reports of suspected related and unexpected SAEs (SUSARs) should be submitted within 15 days and within 7 days for fatal or life-threatening SUSARs, respectively, of the investigator becoming aware of the event, to the Ethics Committee using the CIOMS format.

## **11 ASSESSMENT AND FOLLOW-UP**

### **11.1 RECRUITMENT**

Recruitment will include assessment of in- and exclusion criteria, signing the informed consent, assessment of personal history and a clinical examination.

### **11.2 DAY 1-5 (PHASE 1) AND DAY 1-8 (PHASE 2)**

Baseline evaluation in Zürich as well as the daily evaluation in the other study locations (Davos Wolfgang and Jakobshorn) will consist of a clinical examination, questionnaires, polysomnography, vigilance and psychomotor performance tests and cardiovascular assessments as described above. In study phase 1, there is a defined end of the study after the 5th night of examination and morning physical examination as described above. In study phase 2, there is a defined end of the study after the 8th night of examination and morning physical examination as described above.

### **11.3 FOLLOW-UP**

There is no follow-up.

## **12 Statistics and data analysis**

Completeness, plausibility and distribution of data will be assessed by inspection of numerical results and graphical display. Normality of distribution will be tested by the Kolmogorov-Smirnov statistic. Data will be summarized by means (SD) and medians (quartiles) for normal and non-normal distributions. Effects of treatment and altitude will be evaluated by ANOVA and by multiple regression analysis.

Clinically relevant differences in primary outcomes and corresponding SD are defined as follows according to previous studies: Apnea/hypopnea index: difference 15/h (SD 25/h); prevalence of slow wave sleep relevant difference: 10% of total sleep time (SD 10%); mean reaction time 25ms (SD 30ms); heart rate 10 beats/min (SD 10). Based on these assumptions, power calculation indicates a required sample size of 50 patients to detect clinically relevant differences in primary outcomes with a power of 80% and  $\alpha = 0.05$  (incorporating a Bonferroni correction to account for multiple comparisons). A total of 56 subjects will be recruited to account for potential drop-outs.

Data and all appropriate documentation will be stored for a minimum of 10 years after the completion of the study.

Before analyzing, all data are anonymized by allocating a numerical code to each participant. The code is stored at the principal investigator's office.

